### Data analysis

#### Quantitative analyses

Quantitative analyses will be conducted using SPSS version 23 [39] to explore the variables listed in Table 1. Including the demographics of those asked and not asked, actual registration rates, and whether any differences in these are related to staff group. These analyses will be descriptive in nature and include measures of central tendency. Assessment of baseline recruitment rates to the ODR by the practice (for 1 year prior to the intervention through new patient registration forms) will be compared to the total registration rates in the intervention period. This data will be supplied by the practice administrator.

#### Qualitative analyses

All recorded focus group data will be transcribed verbatim by the investigator and inputted into NVivo 11. Staff online and patient survey responses and training evaluation open questions will be inputted also. All qualitative data captured will be analysed via framework analysis [40]. Framework analysis allows for themes to be compared across the medium they were captured and by their participant group. In this instance, by method (focus group, online survey or training evaluation) and by participants (patients or staff) [40]. Themes will be categorised based on the underpinning theoretical framework for this study, Lau et al.’s (2016) conceptual framework for implementation of primary care interventions and the IIFF Model of Organ Donation Registration [36, 37].

### Ethics and dissemination

#### Consent

As previously specified, formal informed consent will be sought from staff prior to their involvement in training evaluation, focus groups and the online survey, once the intervention has ceased. Informed consent will also be sought from patients prior to their involvement in the online survey. The Information Sheets for each focus group, online survey and consent forms address the key consent principles highlighted by the HRA will ensure participants understand the purpose and nature of the research, what the research involves, its benefits (or lack of benefits), risks and burdens, the alternatives to taking part, how long data will be stored for, that participation is voluntary and that they are able to make a decision on consent at the time of the focus group.

Overt informed consent, to collect and use prompted-choice patient data for the purposes of this research, will not be sought for each patient with whom prompted choice occurs. This is due to the practical difficulties of obtaining formal consent in each consultation, in a working GP practice over a 3-month period. This issue was discussed in-depth with the practice, particularly the patient participation group who approved the use of patient data in this way. The data collected will be gender, age, ethnicity, registration status and organs chosen for donation. Additional data collected concerning the consultation will not be related to the patient and only concern feasibility measures.

#### Anonymity and confidentiality

Focus group discussions will be recorded via digital audio recorder and the transcription of these will be anonymised. Recordings will be stored on encrypted USB in a locked drawer for 5 years before being destroyed. Participants will be informed that all responses will be confidential and anonymised and that responses may be traceable back to the practice in publication. Any quotes published will not refer to participants by name. This will also be stipulated for staff completing the online survey.

#### Distress

For staff and patient well-being, the contact details for bereavement support services will be displayed throughout the practice. Staff will be advised to direct patients to these contact details and staff will be informed that they can refrain from having conversations if it will cause them distress. If staff do not have the conversation for these reasons, this will be recorded to ensure accurate assessment of feasibility can be conducted and take into account the element of distress.

#### Coercion

In the context of joining the organ donation register, it is vital that any patient decision made is elective. Therefore, staff will be trained that, as opposed to normal clinical practice, they are not advising or recommending a patient join the register, merely offering them the opportunity if they wish to. This will be a significant part of staff training and staff will be given scripted examples to help guide them in the appropriate language to use to avoid coercion. Additionally, if they believe the patient may feel under pressure to join, they will be advised to stop the conversation and ask the patient to think about it. As above, if this occurs, it will be recorded on to SystmONE by the GP.

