*Yes – Selected Organs (prompt will be turned off)*
i.
*Yes - Heart*
ii.
*Yes - Liver*
iii.
*Yes - Kidneys*
iv.
*Yes - Corneas*
v.
*Yes - Lungs*
vi.
*Yes - Pancreas*

*Unsure - Patient will think about it (prompt will appear again at next appointment)*

*Do not ask patient again (prompt will be turned off)*

*Patient believes they are already on the register (prompt will be turned off)*
i.
*Would the patient like to re-register?*

*Yes - All organs and Tissues*

*Yes - Selected organs and Tissues*
i.
*Yes - Heart*
ii.
*Yes - Liver*
iii.
*Yes - Kidneys*
iv.
*Yes - Corneas*
v.
*Yes - Lungs*
vi.
*Yes - Pancreas*

*No - Patient would not like to re-register*

f.
*Patient was not asked*
i.
*Not appropriate for consultation*
ii.
*Lack of time*
iii.
*Clinician personal beliefs (only select if personal view of clinician NOT situational factor)*
iv.
*Other reason, please specify*

If staff member presses ‘No’ on the prompt, this indicates they have not or will not ask the patient to join the NHS ODR. They will then be instructed to complete the following questionnaire which records reason why the patient was not asked.g.
*Patient was not asked. Reason why patient was not asked:*
i.
*Not appropriate for consultation*
ii.
*Lack of time*
iii.
*Clinician personal beliefs (only select if personal view of clinician prevents patient being asked)*
iv.
*Other reason, please specify*

It was highlighted that staff may select the ‘Yes’ questionnaire at the beginning of a consultation but be unable to carry out prompted choice as the consultation progresses. To allow staff to record that the patient was not asked under these circumstances question f. was included in both the ‘Yes’ and ‘No’ questionnaire.

To ensure no untrained staff ask patients about organ donation, the prompt will only appear for staff who have received the training and only for patients aged 18 or over. If prompted choice has previously been completed for the patient and the patient responded “Yes”, “Do not ask patient again” or “Patient believes they are already on the register”, the prompt will switch off and the patient will not be asked again at subsequent appointments.

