### Registration data

The data to be collected through SystmONE can be viewed in Table 2. Any leaflet registrations collected in the practice will be included in registration data analysis. However, it is possible that patients may register on the NHS ODR and post these forms themselves. Therefore, registration by leaflet data, collected at reception, will be treated with caution during analyses and interpretation.

**Table 2 Tab2:** Registration data to be collected by SystmONE

Variable	Response format
Registration type	SystmONE/Paper
Date of consultation	Dd/mm/yy
Patient age	Years
Patient ethnicity	ONS categories
Patient gender	Male or female
Patient asked	Yes/no
Reason patient not asked	Not appropriate/time/clinician personal beliefs/other (free text)
Patient joined NHS ODR	Yes/no/patient believes already on register
Organs selected	All/kidneys/heart/liver/corneas/lungs/pancreas
If no, which response	Unsure/do not ask again
Patient believes already on register. Re-register	Yes/no
Organs selected	All/kidneys/heart/liver/corneas/lungs/pancreas
Staff group	Doctor/Nurse/Healthcare Assistant

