### Data management

Data will be accessed through SystmONE at the practice by the investigator. Only data relevant to the study (i.e. the data specified in Table 2) will be accessed. Data will be anonymised by the investigator and exported from SystmONE for analysis on an encrypted memory stick. Paper consent forms and training evaluation forms will be stored in a locked filing cabinet at the University of Bedfordshire with access only available to the investigator. These will be stored for 5 years. Online staff survey data will be securely hosted on Qualtrics, who adhere to the data protection act, the general data protection regulation and online data protection procedures. At no point will participants be asked their name, and the only identifiable data collected by Qualtrics will be participants IP address. This will be deleted in all data sets extracted for analysis.

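### A conversation stopped for possible pressure can be entered on SystmONE, but no entry both counts the patient as asked and shows the stop, so use of this safeguard cannot be counted

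*Protocol article*

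**What the plan says.** All places are in the protocol article.

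- **Coercion.** If staff believe a patient may feel pressed to join, "they will be advised to stop the conversation and ask the patient to think about it". The next sentence is the recording commitment: "As above, if this occurs, it will be recorded on to SystmONE by the GP".
- **Distress**, the section just before it, also promises recording. For conversations that staff do not hold because of distress, "this will be recorded to ensure accurate assessment of feasibility can be conducted and take into account the element of distress".
- **Prompted choice** prints the questionnaire item by item. One response reads "Unsure - Patient will think about it (prompt will appear again at next appointment"). The item for a patient who was not asked appears in both questionnaires. It was put into the *Yes* questionnaire for consultations in which staff press *Yes* but then cannot go through with the question: "To allow staff to record that the patient was not asked under these circumstances".
- **Registration data, Table 2.** A patient who did not join is classed as "Unsure/do not ask again". The reason for not asking is "Not appropriate/time/clinician personal beliefs/other (free text").
- **Data management.** "Only data relevant to the study (i.e. the data specified in Table 2) will be accessed".

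**The concern.** Stopping the conversation is one of the plan's protections against pressure, and it is the one that applies once the subject has been raised. Prompted-choice data are collected without individual consent (Consent section), and acceptability is part of the stated objective. How often clinicians felt they had to stop is therefore worth knowing, and the plan says that the event goes into the clinical system. The printed form and Table 2 nevertheless provide no entry by which a stop can be recognised afterwards. The study would hold the records but could not say how many were stops, and the count of undecided patients would contain some whose conversation the clinician ended.

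**Working it through.** No figure of the plan is at issue, so the check sets the recording commitment against every entry that the form and Table 2 allow.

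**Entries counted from the document**

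| Place | Entries | Number | Identify a stop |
|---|---|---|---|
| Form, patient asked | yes to any organ; yes to selected organs; unsure; do not ask again; believes already registered | 5 | 0 |
| Form, patient not asked | not appropriate; lack of time; clinician's beliefs; other | 4 | 0 by name; *other* takes free text |
| Table 2, if patient did not join | unsure; do not ask again | 2 | 0 |

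Table 2 has 13 rows, most of which (age, date, organs and so on) could never hold this event. One row takes free text, the reason for not asking, and it applies only when the patient is coded as not asked.

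**What each possible entry does to a stop**

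| Entry chosen | Counted as asked? | Shows the stop? | Prompt afterwards |
|---|---|---|---|
| *Unsure* | yes | no | returns at next appointment |
| *Do not ask patient again* | yes | no | switched off |
| Not asked, *other*, free text | no | yes, if staff write it | not stated |

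No row has yes in both middle columns.

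**Consequence for the counts.** Let u be the number of ordinary undecided patients and s the number of stops entered as *Unsure*. The study observes only

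n(Unsure) = u + s.

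That is one total with two unknowns, so s cannot be recovered. The number asked and the number registered are unaffected by this route, so the registration rate among those asked does not move.

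If the question has already been put and staff use the free-text route instead, each such patient moves from asked to not asked. The Quantitative analyses section describes the demographics of those two groups. If the stop comes before the question is put, *not asked* is the correct code and the free text can carry the reason.

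**Could the information come from elsewhere?** A note in the patient's record lies outside Table 2, and the study reads only Table 2 data. Training could tell staff which box to tick, but none of the existing boxes does both jobs. Focus groups and surveys may yield accounts of stopped conversations, but not a count.

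**The case against.** The strongest reply is that the commitment, read plainly, is kept. Staff are told to leave the patient to think it over, and the *Unsure* response is worded almost identically. The Coercion section promises a record; it does not promise that stops will be counted or reported apart. This stands. A reader might infer that the plan contradicts itself or that the event cannot be recorded at all, and the text supports neither.

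Four further objections also hold:

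- A reader might say that the study fails its own stated purpose for recording. That purpose appears in the Distress section, for conversations not held. Carrying it over to stopped conversations depends on how the opening words of "As above, if this occurs, it will be recorded on to SystmONE by the GP" are read, so it is an inference.
- A reader might treat the free-text route as miscoding in every case. It is miscoding only when the question had already been put.
- A reader might see the returning prompt as a harm. It suits a patient who was asked to think, and staff keep their discretion not to ask.
- Stopping is not the only protection. Training to offer rather than advise, and scripted language, come first in the same section.

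It is also fair that this is a descriptive, single-practice feasibility study with qualitative components that may bring pressure to light. What the objection leaves untouched is that stops are not separately identifiable, which the entries themselves show.

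**Conclusion.** The point holds as a minor, inexpensive improvement. A stop for possible pressure can be entered, but not in a way that both keeps the patient among those asked and shows what happened. Use of the safeguard therefore cannot be counted, and such stops are mixed with ordinary undecided patients.

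The size is limited to what the entries show: 0 of 5 asked responses, 0 of 4 not-asked reasons by name, and 0 of 2 levels for patients who did not join. The document gives no basis for estimating how many stops will occur, and they may be rare. No stated figure changes.

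The conclusion assumes that the printed questionnaire and Table 2 are the form and data set in use, as their item-by-item presentation and the Data management section indicate.

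The reference to the GP alone is loose wording and adds no weight: the Prompted choice section has four staff groups asking (GPs, nurses, healthcare assistants, other clinical professionals).

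**What to change.** - Add one response to the *Yes* questionnaire, and the same level to Table 2 under the row for patients who did not join (2 levels become 3): *Conversation stopped: patient may feel under pressure*. Count the patient as asked.
- Name this entry in the Coercion section, and report its number separately from *Unsure* and *Do not ask patient again*.
- Keep the prompt behaviour now attached to *Unsure*: it returns at the next appointment and staff use their discretion.
- As a wording correction only, have the Coercion section say that the entry is made by the staff member who asked.

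**Cost.** One more response on a SystmONE template already adapted for the study, one table level, one line in training and one reworded sentence. The form becomes slightly longer, and the Discussion already worries that staff may not complete it. The ethics committee may need a notice, because the Consent section says that the additional consultation data do not concern the patient, whereas this entry records how a patient may feel.

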#### Impact on normal running of the practice

The intervention will be mindful of the normal running of the practice. Ensuring the impact on the working practice is minimal has been achieved by collaborating with the practice and patient group throughout the design. Staff will be informed that the priority is patient care, and the intervention should always come second.

#### Dissemination policy

Research findings will be presented in various publications throughout this study. Namely, conference presentations, academic journals and media releases. The intention being is to inform future researchers of the success of implementing an organ donation intervention in a general practice setting.

## Discussion

Membership of the NHS ODR is the primary way to express organ donation wishes in the UK [1]. Interventions to target this are vital in reducing the discrepancy between the number of people donating their organs after death and those on the transplant list [1]. Currently, there is no location in the UK where people are routinely asked if they would like to join the NHS Organ Donor register. This study proposes general practice could be this location. However, the NHS is currently experiencing significant challenges [16]; therefore, an assessment of feasibility is essential before examining if this intervention would increase NHS ODR membership.

A limitation of this research is the lack of incentives for both the GP practice as a whole and for the individual participation of staff and patients in prompted choice. Introduced in 2004, the Quality Outcomes Framework (QOF) provides practices with financial reimbursement for each patient asked about a variety of health problems; for example smoking cessation [41]. Therefore, the lack of incentive in the current intervention may decrease the likelihood of staff completing the intervention form, including the elements concerning feasibility (e.g. reasons for not asking patients) and reduce the data captured using this method. Focus groups and online surveys could help examine the impact of this on the intervention; however, recruitment to these may also be impacted by the limited incentives (lunch for staff).

A key ethical concern when developing this research is the issue of distress to patients and staff during organ donation conversations. Predicting who might become distressed by the prompted choice conversation is challenging. To help ensure as minimal distress to patients occurs as possible, staff will be trained in how to best have these conversations by the experienced specialist organ donation nurse training division, a part of NHS Blood and Transplant. These staff have these conversations daily with grieving families and will help guide staff in this. Additionally, staff will be informed that they must use their professional judgement as to whether a conversation is appropriate for the patient they are about to see. If staff are unsure, they will be instructed to refrain from asking the question.

In contrast, a strength of the proposed study is the current lack of investigation of UK general practice to target organ donation registration [16]. The contribution to knowledge therefore will be to examine if general practice is appropriate for this. A further strength is the involvement of the GP practice throughout the development of the intervention and data collection. Additionally, the study is underpinned by strong theory and methodology. Intervention Mapping is a well-respected method of intervention development and allows the integration of behaviour change theory into interventions an important and often neglected step by intervention developers [35]. Throughout the process, Lau et al.’s conceptual framework was used to design the implementation of the intervention. This framework specifies the importance of context within implementation and provides overt recommendations specifically tailored to the primary care setting [37]. The IIFF model, also used to underpin the intervention, was developed iteratively from interventions designed to increase organ donor registrations. It provides a practical specification for intervention compared to other socio-cognitive models of behaviour change which has more abstract components which are difficult to translate into actual interventions ([42]; e.g. self-efficacy, social norms, attitudes and intention from the Theory of Planned Behaviour TPB).

Finally, the study described in the present protocol is the first of two studies to examine the feasibility of this organ donation intervention in UK general practice. Initial exploration in a single GP practice allows for refinement of the intervention using Intervention Mapping prior to further feasibility testing. The findings from this study will inform a multi-centre feasibility cluster randomised controlled trial, which will aim to explore the recruitment of GP practices and collect data to perform a sample size calculation for full randomised controlled trial.

## Abbreviations

CAG: Confidentiality Advisory Group
HRA: Health Research Authority
IM: Intervention Mapping
NHS ODR: NHS Organ Donor Register
NHS REC: NHS Research Ethics Committee
NHSBT: NHS Blood and Transplant
PPG: Patient Participation Group
QOF: Quality Outcomes Framework
SNOD: Specialist Nurse in Organ Donation
SPIRIT: Standard Protocol Items: Recommendations for Interventional Trials
TPB: Theory of Planned Behaviour
